#### Dissemination and translation

We propose to present the findings from this study to Victorian and Australian policymakers at relevant national conferences, in person to the Victorian Government Department responsible for MCH nursing, at international IPV and nursing conferences, in peer-reviewed and professional journals.

### Two year follow-up

We propose to seek permission to obtain routine data for screening inquiry, safety plans and referrals for IPV two years after the MOVE implementation completion. We will also aim to conduct a survey with all nurses in the two arms of the MOVE trial to investigate the sustainability of the screening intervention, using NPT constructs. Analyses of these data will be conducted as outlined above.

## Discussion

MOVE will be the first randomised trial to determine IPV screening effectiveness in a community based nurse setting and the first to examine sustainability of an IPV screening intervention. Screening for IPV remains a controversial area, but governments especially in high and middle income countries continue to implement screening policy in health care settings, without addressing the key barriers reported by primary care professionals, especially workloads, ongoing training and lack of effective multi-agency collaboration. Without addressing such barriers, there is doubt about the sustainability or effectiveness of screening [27]. Normalisation Process Theory [36] has been developed to support sustainability of implementation and evaluation of complex interventions and complex settings and is appropriate to the effectiveness and sustainability questions addressed by the MOVE trial.

This study is being conducted in Victoria, Australia where legal sanctions and strong family violence policies exist at national and state level. As a high income country crisis and outreach responses for women are funded and supported (although stretched to meet need), improved policing responses and intervention/protection orders available from magistrates courts tailored to family violence victims are also available. There are also behaviour change groups for male perpetrators and services for children who have experienced family violence. In this context, when primary care providers identify women experiencing family violence, services exist to support women and sanctions are available (however limited) to prevent further harm. As a result of previous training conducted in the MOSAIC study and the further training offered in the new Victorian Key Ages and Stages initiative, MOVE nurse teams in both arms of this study have been well trained to screen and refer women experiencing violence. Of all Victorian MCH nurses, nurses in this study are well prepared and the intervention arm nurses even better prepared, following their active involvement in developing a good practice model.

MOVE results will further inform the debate about the effectiveness of IPV screening and describe IPV prevalence in a community based post-partum and early infant population.

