## Abstract

**Background:**

Intimate partner violence (IPV) can result in significant harm to women and families and is especially prevalent when women are pregnant or recent mothers. Maternal and child health nurses (MCHN) in Victoria, Australia are community-based nurse/midwives who see over 95% of all mothers with newborns. MCHN are in an ideal position to identify and support women experiencing IPV, or refer them to specialist family violence services. Evidence for IPV screening in primary health care is inconclusive to date. The Victorian government recently required nurses to screen all mothers when babies are four weeks old, offering an opportunity to examine the effectiveness of MCHN IPV screening practices. This protocol describes the development and design of MOVE, a study to examine IPV screening effectiveness and the sustainability of screening practice.

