**Discussion:**

MOVE will be the first randomised trial to determine IPV screening effectiveness in a community based nurse setting and the first to examine sustainability of an IPV screening intervention. It will further inform the debate about the effectiveness of IPV screening and describe IPV prevalence in a community based post-partum and early infant population.

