### The Victorian maternal and child health service and the context for IPCV screening

Victorian maternal and child health nurses (MCHNs) are trained nurse midwives who visit over 95% of all Victorian mothers with newborns at home and continue to offer support at their local centres until the children are six years old [24]. This free, universal, comprehensive primary health-care service aims to provide health promotion, illness prevention, early detection of developmental problems, and intervention to enhance the health and wellbeing of young children and their families. Australia has three tiers of government: federal or national; state (or territory) and local government or council. MCHN nursing is located and managed in the complex local government environment, while implementing policies formulated at state government level. They are often funded at local government level (usually 60% local government and 40% state government).

In late 2009, just as this proposed trial of IPV screening versus usual care was funded, a new comprehensive approach to screening children and their mothers for other common problems and developmental delays, Key Ages and Stages (KAS), was introduced into Victorian maternal and child health nursing practice [25]. Under the new Key Ages and Stages protocol, MCHNs are now required to screen all mothers for family violence - the government’s preferred term, which includes child abuse (not only IPV) - when their babies are four weeks old. MCHNs were provided with three hours training to use a Common Risk Assessment Framework, offering a common definition of IPV for health care providers, police, family violence services and courts, symptoms to look for and referral processes. Included in KAS strategies were computer prompts for the now mandated four week IPV screening, any screening at a later consultation, and the requirement to report regular data about IPV screening, safety plans and referrals and other child health screening and referral rates to government.

Nurses are required to ask the following questions about family violence:

1. Are you in any way worried about the safety of yourself or your children?

2. Are you afraid of someone in your family?

3. Has anyone in your household ever pushed, hit, kicked, punched or otherwise hurt you?

4. Would you like help with this now?

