### MOSAIC (MOtherS' advocates in the community)

Prior to this government initiative, in our previous IPV trial of non-professional mother-to-mother support for pregnant or recent abused mothers, known as MOSAIC [26], MCH nurses struggled to identify and refer clients experiencing violence despite comprehensive six-hour training by a domestic violence training agency and additional resources (referral booklets, posters etc.). An impact evaluation conducted at the end of the study, showed that 66% of nurses said that they were comfortable or very comfortable asking about partner violence, while 18% remained uncomfortable. Thirty-five percent cited partners or family members being present as the major obstacle to asking about IPV, followed by fear of embarrassing women (14%) and the need to focus on the child as their priority (13%). When asked what made it difficult, 42% of nurses said women's reluctance to take further steps, referral agencies’ waiting lists (22%) and the difficulty of finding support for women with special needs (17%). When asked what should be put in place to assist other nurses to develop their skills and increase their confidence in this area, nurses suggested regular training (1); MCHN specific clinical guidelines for IPV (2); and an MCHN clinical pathway (3).

Following on from MCHN feedback in MOSAIC, this study originally aimed to compare implementation of IPV screening with usual care; however with the introduction of mandatory IPV screening of all recent mothers when babies are four weeks old, the trial design was modified to evaluate an enhanced model of IPV screening addressing some of the identified challenges for nurses and addressing the issue of sustainability, compared with basic mandatory IPV screening.

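### The headline claim to determine whether IPV screening works is wider than the randomised comparison, which is enhanced against basic mandatory screening

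*Protocol article*

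**What the plan says.** **The headline.** The closing paragraph of the abstract and the opening of the Discussion make the same claim: "MOVE will be the first randomised trial to determine IPV screening effectiveness in a community based nurse setting". The abstract adds: "It will further inform the debate about the effectiveness of IPV screening", and the Discussion ends on the same note. The abstract's Background is softer and calls MOVE "a study to examine IPV screening effectiveness and the sustainability of screening practice".

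**The comparison.** The section on MOSAIC records that "this study originally aimed to compare implementation of IPV screening with usual care". After the state mandate, "the trial design was modified to evaluate an enhanced model of IPV screening addressing some of the identified challenges for nurses", and this is to be "compared with basic mandatory IPV screening".

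**What the comparison arm receives.** The section on the Victorian service says that "MCHNs are now required to screen all mothers for family violence" when babies are four weeks old. It also describes three hours of training, computer prompts and required reporting. The Discussion adds that "MOVE nurse teams in both arms of this study have been well trained to screen and refer women experiencing violence".

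**The concern.** The comparison was changed and the headline claim was not. A trial of screening against usual care could speak to whether screening is effective. A trial in which both arms must screen can speak only to what the enhanced model adds.

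This matters because of the audience. The article calls screening controversial, notes that governments continue to adopt it as policy, and plans to present the findings in person to the state department responsible for these nurses. Under the headline as written, a null result could be taken as evidence that screening does not work, when it would show only that no gain over mandated screening was detected. A positive result could be credited to screening in general rather than to the package.

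**Working it through.** No plan figure bears on this point, so the check sets the passages side by side.

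1. **What counts as screening.** The section on screening for IPV defines it as routine, systematic inquiry of all presenting women with a consistent set of questions.

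2. **Does the comparison arm meet that definition?** The mandate covers all mothers at four weeks with a fixed set of four questions. It applies to Victorian maternal and child health nurses generally, and nothing in the article exempts either arm. By the article's own definition, both arms are screening arms.

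3. **What differs by arm.** The intervention sections list:
   - a woman-focused visit at three months, or fifteen minutes added to the four-month visit;
   - a self-completed maternal health checklist with two further questions;
   - guidelines and a clinical pathway;
   - nurse mentors;
   - family violence liaison workers.

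4. **What the contrast identifies.** Write μ_N, μ_B and μ_E for the mean outcome under no screening, basic mandated screening and the MOVE model. Then

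   μ_E − μ_N = (μ_E − μ_B) + (μ_B − μ_N).

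   The trial observes arms with means μ_E and μ_B, so it estimates μ_E − μ_B. No arm has mean μ_N. Any observed value of μ_E − μ_B, including zero, is compatible with any value of μ_B − μ_N.

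5. **Could a difference in actual inquiry rates recover the screening effect?** A mandate is not the same as delivery, and the first primary outcome looks for a 15% increase in women being asked. Actual exposure to screening may therefore differ by arm. Using allocation as an instrument for being asked would require that the package affects disclosure and referral only through asking. The checklist format, extra questions, visit timing, mentors and liaison workers are meant to act on disclosure and referral directly, so that condition is not credible here.

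6. **Does the rest of the plan follow the revised contrast?** Yes. The abstract's Methods describe a trial of a good practice model. The Aims ask whether nurses using that model do more than comparison nurses. The primary outcomes and the list of primary comparisons are differences by arm in inquiry, disclosure, safety plans and referral.

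7. **Another trace of the former contrast.** The survey sample size section takes its predicted 15% increase in disclosure from a study of screening against usual care. This fits the view that the text was only partly updated. Whether that effect size suits the present contrast is a separate question, and nothing here rests on it.

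**The case against.** The strongest reply is that the working parts of the protocol already ask the right question. The change of comparator is disclosed, and the aims, outcomes and analysis follow it. A reader of the Discussion is told that nurses in both arms are trained to screen. Further informing a debate is also a modest phrase, which evidence on enhanced against basic screening can meet. All of this stands. There is no hidden comparator, and nothing in the design or analysis needs to change.

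A second reply is that screening effectiveness may mean how well nurses deliver screening. That is plausible for the abstract's Background, which first mentions the mandate and then speaks of nurses' screening practices. It does not rescue the claim in the abstract's closing paragraph and the Discussion. The section on screening frames the controversy as whether screening is effective and should be recommended, and the Discussion moves from its claim straight to government screening policy.

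Three stronger readings are tempting and are not supported:
- **That a null will be misreported.** The article sets no such reporting rule and commits only to named differences by arm. Misreading is a risk, not a certainty.
- **That the two arms are equally screened.** The first primary outcome expects inquiry to differ.
- **That no result bears on benefit to women.** Satisfaction with care is an aim and a secondary outcome compared by arm. Reported harm from being asked is also to be given by arm, and the survey collects depression, anxiety and motherhood measures. These contrasts are still enhanced against basic screening, but a blanket disclaimer would be inaccurate.

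**Conclusion.** The point holds as an overstated headline conclusion. The abstract's closing paragraph and the Discussion, and less clearly the abstract's Background, promise an answer on screening effectiveness. The randomised contrast supports only a statement about what the MOVE package adds to mandated screening.

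The size is a matter of scope, not of a number: none of the two arms is unscreened by design, so the trial gives no randomised estimate of screening against no screening. This rests on the mandate applying to all eight teams, as the article describes, and on the article's own definition of screening. It needs no assumption about effect sizes. The correction is worth making before results are reported because it changes what the trial may be said to conclude.

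**What to change.** In the abstract's closing paragraph and in the Discussion, replace the claim about determining screening effectiveness with: *to determine the effectiveness of an enhanced nurse IPV screening model compared with basic mandatory four-week screening*. Align the purpose statement in the abstract's Background with this.

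Add one sentence in the Discussion: *Neither a positive nor a null difference between arms estimates the effect of screening versus no screening.*

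The aims, outcomes, analysis and data collection stay as they are. The cost is a few words and a narrower headline claim.
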